### Criteria for discontinuing allocated interventions

Any undesirable experience (of either a physical or psychological nature) occurring to a participant during the study, whether or not considered related to undergoing treatment with SF or placebo, will be considered an adverse event (AE). Participants will be asked for AEs at each visit and then will be discussed with the study physician at the site. Thus, if an AE occurs in response to SF or placebo, this will immediately be recorded by the principal investigator (PI) or the PI’s staff, and the participant may be discontinued from the study.

Serious adverse events (SAEs), serious adverse reactions (SARs) or unexpected serious adverse reactions are defined, respectively, as any adverse event, reaction, or unexpected adverse reaction that results in death; is life-threatening and/or requires hospitalization or prolongation of existing hospitalization; results in persistent or significant disability or incapacity; or consists of a congenital anomaly or birth defect. Any of them will be communicated immediately to the lead coordinator of the trial at Vall d’Hebron Research Institute (VHIR) and to the coordinating PI at the clinical site, who will be responsible for reporting the event to the ethics committee that approved the protocol. Suspected unexpected serious adverse reactions (SUSARs) that are fatal or life-threatening must also be reported not later than 7 days after the sponsor is first made aware of the reaction. Any additional relevant information must be reported within 8 days. SUSARs that are not fatal or life-threatening must be reported within 15 days of the sponsor first becoming aware of the reaction. All ongoing AEs will be followed up until no more signs and symptoms are verifiable or until stability has been reached. Depending on the event, additional tests or medical procedures, as well as referrals to a general physician or a medical specialist, will be indicated during this follow-up phase.

In the case that a participant’s psychological state deteriorates to a clinically significant degree during the trial, the investigators will either discuss with the participant the possibility of withdrawing from the study or decide that the participant should withdraw. If a participant, for any reason, requires treatment with certain therapeutic agents (i.e., antibiotics), the agent taken and time of administration will be noted. If any other protocol exclusion violation has occurred, the participant’s involvement will be discontinued. Participants may at any time request to be withdrawn from the study or revoke their consent to participate. If a patient is discontinued from the trial, a follow-up visit will be carried out to ensure the well-being of the participant.

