Recruitment began on 22 February 2019 and will have a duration of 2 years. A total of 180 participants (60 subjects per site) will be recruited by trained psychiatrists and/or psychologists at the different sites (see Fig. 1). Strategies aimed at optimizing the recruitment process will include the distribution of handouts or flyers to colleagues, physicians, and families, as well as an offer of reimbursement of study-related travel costs to participants. Furthermore, and depending on local regulations, information via presentations, websites, and social media campaigns will be provided. Regular calls will be made to patients to avoid participant withdrawal from the study.

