Trial-specific assessments will be done at T0 (duration, approximately 3 h), scheduled within 1 week after TS. During the week between TS and the baseline visit (T0), the mobile health system will be used at home. Here and during 24 h, participants will wear movement sensors on two working days and on Saturday and Sunday, and they will be asked to complete three 24HDRs on a web-based tool or paper on two nonconsecutive weekdays and one weekend day (duration, 15 min each). Individuals will also be asked to collect feces on one day during the 1-week period at home and to bring it along at T0.

In addition to responding to the questionnaires and scales listed in Table 1, participants will be instructed on how to store and eat the study product (SF or placebo). The intervention will begin on the day after T0, and participants will be asked to continue with their usual medications and/or treatments. Participants will have to complete another three 24HDRs, collect their feces before the next visit, and bring it along at T1, following the same guidelines as during the screening assessments.

T1 (midintervention assessment; duration, approximately 3 h) will take place 5 weeks after T0. This midintervention assessment aims at obtaining the primary and secondary outcome measures during the ongoing trial. Participants will be asked once again to wear movement sensors, complete another three 24 HDRs, and collect their feces 1 week before T2 and bring it along at T2. At 10 weeks after initiating the probiotic or placebo intervention (T2), primary and some secondary outcome measures will be assessed again (duration, approximately 3 h).

Within 1 week after T2 and with the aim of measuring safety aspects of the intervention (i.e., somatic complaints/side effects as well as gastrointestinal symptoms), the follow-up (T3) assessment will take place (duration, approximately 20 min).

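### As described, adverse events are actively asked for at visits about five weeks apart during dosing; the calls already planned could ask too, at little cost

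*Protocol article*

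**What the plan says.** The protocol article, under Criteria for discontinuing allocated interventions, defines an AE broadly: "Any undesirable experience (of either a physical or psychological nature) occurring to a participant during the study". It then says when AEs are sought: "Participants will be asked for AEs at each visit and then will be discussed with the study physician at the site". On handling, it says that "if an AE occurs in response to SF or placebo, this will immediately be recorded by the principal investigator (PI) or the PI’s staff", and of serious events that "Any of them will be communicated immediately to the lead coordinator of the trial".

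The same section requires action if a participant's "psychological state deteriorates to a clinically significant degree during the trial": withdrawal is either discussed or decided. It also requires that, if a participant needs an agent such as an antibiotic, the agent and its timing are noted. A patient who is discontinued gets a follow-up visit.

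The schedule (Table 3, Participant timeline) places T0 on day 1, T1 on day 35 ± 2, T2 on day 70 ± 2 and T3 on day 77 ± 2. It has no row for telephone contacts. The text agrees that T1 "will take place 5 weeks after T0".

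Calls appear once, in Study population and recruitment: "Regular calls will be made to patients to avoid participant withdrawal from the study". Their frequency, content and caller are not given.

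**The concern.** The plan acts on three things that can happen on any day of a roughly ten-week dosing period: AEs, clinically significant psychological deterioration, and antibiotic use. The active inquiry it describes takes place at visits about five weeks apart. In between, the described process depends on the participant coming forward or on recall at the next visit.

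- **Deterioration.** Participants are selected for a CGI-S score of at least 4, an ARI of at least 5, and ADHD and/or BPD. Prompt action on deterioration presupposes that someone notices it.
- **Tolerability.** Short-lived gastrointestinal or somatic complaints early in an interval would be recalled some five weeks later. This tends to lower AE counts in both arms and makes the tolerability comparison less precise.
- **Antibiotics.** Recent antibiotic treatment is an exclusion criterion, and stool is sampled at T1 and T2, so the dates of any course bear on the microbiome results.

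The calls are contacts the trial already intends to make. As described, they do not put the safety question.

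**Working it through.** **Inputs.** Visit days and windows are from Table 3: T0 = day 1; T1 = day 33 to 37; T2 = day 68 to 72; T3 = day 75 to 79.

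**Formula.** Shortest gap = earliest day of the later visit − latest day of the earlier visit. Longest gap = latest day of the later visit − earliest day of the earlier visit.

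| Interval | Shortest | Nominal | Longest |
|---|---|---|---|
| T0 to T1 | 33 − 1 = 32 | 35 − 1 = 34 | 37 − 1 = 36 |
| T1 to T2 | 68 − 37 = 31 | 70 − 35 = 35 | 72 − 33 = 39 |
| T2 to T3 | 75 − 72 = 3 | 77 − 70 = 7 | 79 − 68 = 11 |

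The plan's own figure, five weeks (35 days) from T0 to T1, lies within 32 to 36 days and is reproduced. The 39-day maximum applies to T1–T2 alone and needs both visits at opposite ends of their windows. About five weeks is the typical gap.

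**Contacts during dosing.** Dosing starts the day after T0, and T2 marks ten weeks. Scheduled AE inquiry in that period therefore takes place at two visits, T1 and T2. T3 follows the end of the ten-week intervention, so it can collect earlier events but cannot prompt action during treatment.

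**Other routes between visits.** The structured side-effect questions are scheduled at T1, T2 and T3. The clinician's severity rating and medication evaluation after baseline are scheduled at T1 and T2. The mobile system is described as sharing physical-activity data (acceleration and steps), not symptoms. The remaining contact is the calls, with retention as their stated aim.

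**Antibiotics.** The entry criterion looks back 6 weeks, which is 6 × 7 = 42 days. The longest between-visit gap is 39 days, which is less than 42. Any course taken between two visits would thus fall within that look-back period before the next visit, when stool is sampled.

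**What cannot be computed.** The article gives no call frequency, so the interval that would result from asking about AEs on the calls is unknown. Nor does it give an AE rate from which to estimate under-recall.

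**The case against.** The strongest reply is that this is a condensed article. It does not say that AEs are sought at visits and nowhere else, it does not say that the calls leave out safety questions, and it does not prevent participants from reporting events themselves. The full protocol, which is not shown, may specify the content of the calls. That stands as a limit: the point concerns the rule as described. It does not remove the point, because the article states a positive rule for when AEs are asked for and prints a full schedule that agrees with it.

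A reader might infer four stronger things, which the documents do not support.

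- **That the plan contradicts itself by requiring immediate recording.** It does not. Immediacy governs how an event is handled once known, and the recording sentence is worded for AEs in response to the product. Asking at visits and acting at once on what becomes known are compatible. The reporting clocks that run from sponsor awareness are likewise no defect.
- **That events between visits are lost.** This is not shown. Body-system questions and the Bristol Stool Scale are repeated at T1, T2 and T3; perceived stress, stressors and medication are reviewed at T1 and T2; and ongoing AEs are followed to resolution or stability. These prompts reduce poor recall, although they do not bring detection forward.
- **That participants who stop before T1 provide no solicited AE data.** A follow-up visit is planned for discontinued patients, and AEs are asked for at each visit. A gap remains for those who do not attend, whom calls might not reach either.
- **That antibiotic use needs real-time action.** The plan asks that it be noted, and the medication evaluation at T1 and T2 can do that. What calls would improve is the dating.

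It can also be said that the product is described as generally regarded as safe and that participants continue usual care, so visits five weeks apart may be adequate. The documents do not show otherwise. This limits the weight of the point, but it does not argue against a better use of contacts already planned.

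**Conclusion.** The point holds as a low-cost improvement to safety ascertainment. As described, active AE inquiry during dosing falls 32 to 36 days after T0 and then 31 to 39 days after T1. Between those visits, AEs, psychological deterioration and the dates of antibiotic use reach the site through volunteering or later recall. The likely effect is late detection and some under-recall in both arms; the documents give no basis for putting a number on it. No effect on the primary outcome or its analysis is claimed.

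The conclusion assumes that the article's AE rule and Table 3 reflect the full protocol, and that the calls do not already ask about safety. If they do, one clarifying sentence settles the matter.

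**What to change.** In Criteria for discontinuing allocated interventions, change the rule so that AEs are asked for at every visit and at every planned telephone call. Give the calls a short fixed script, identical in both arms, covering:

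- new symptoms or hospital contact;
- new medicines, including antibiotics, with dates;
- current psychological state.

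Enter the answers in the AE and medication log and pass them to the site study physician under the process already described. State the call frequency, so that the resulting interval between safety contacts is known. This changes ascertainment only; it alters no dose and no rule for stopping or withdrawing.

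The cost is one revised sentence, one form and, by assumption, a few minutes per call. More frequent asking will probably raise AE counts slightly. An identical script in both arms keeps the comparison fair, but the counts will be less comparable with those of trials that ask at visits alone.

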### Outcome measures

#### Primary outcomes

The primary outcome measure will be response to treatment, defined by a reduction in the Affective Reactivity Index–Self-Report (ARI-S) scale total score of at least 30% compared with baseline plus a Clinical Global Impression–Improvement Scale total score of 1 or 2 (very much improved or much improved) at the end of the placebo-controlled phase.

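### Stopping the study product is merged with leaving the study, and no week-10 CGI-I or ARI-S assessment is provided for those who leave

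*Protocol article*

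**What the plan says.** All rules on stopping are in the protocol article, section Criteria for discontinuing allocated interventions. The heading concerns the intervention; the text concerns the study.

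- **Adverse event in response to the product:** "the participant may be discontinued from the study". This is discretionary.
- **Clinically significant psychological deterioration:** "the investigators will either discuss with the participant the possibility of withdrawing from the study or decide that the participant should withdraw".
- **Antibiotics:** "the agent taken and time of administration will be noted". No exit is stated.
- **Other violations:** "If any other protocol exclusion violation has occurred", the person's involvement ends. No discretion is stated.

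Two contacts are provided afterwards. One is a visit: "If a patient is discontinued from the trial, a follow-up visit will be carried out to ensure the well-being of the participant". The other is safety follow-up: "All ongoing AEs will be followed up until no more signs and symptoms are verifiable or until stability has been reached".

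The section Primary outcomes defines response as a fall of at least 30% in ARI-S plus a CGI-I of 1 or 2, "at the end of the placebo-controlled phase". The section Participant timeline places this at week 10: "At 10 weeks after initiating the probiotic or placebo intervention (T2), primary and some secondary outcome measures will be assessed again". Table 3 also schedules both scales at T1 (week 5) and T3 (week 11).

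**The concern.** Nothing in the text lets a participant stop taking the product and remain in outcome follow-up. The record-and-continue approach used for antibiotics is not extended to the other events.

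The triggers are post-randomization events that may be related to treatment or to the endpoint. Someone withdrawn for psychological deterioration is unlikely to be rated much improved at week 10, so that exit is tied to the outcome. Product-related adverse events may differ between arms: the active sachet contains four fermentable fibers at 2.5 g each and the placebo is maltodextrin (section Randomization and study intervention).

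If week-10 values are missing for such reasons, the observed comparison can drift from the randomized one, and the trial loses precision. A later analysis plan can choose assumptions about missing values, but it cannot supply week-10 ratings that were not taken.

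**Working it through.** **1. Does the text provide the primary outcome for leavers?**

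| Route out | Study participation | Contact stated afterwards | Week-10 CGI-I and ARI-S stated |
|---|---|---|---|
| Product-related adverse event | may end | well-being visit, adverse-event follow-up | no |
| Psychological deterioration | withdrawal discussed or decided | same | no |
| Other exclusion violation | ends | same | no |
| Antibiotic use | no exit stated | scheduled visits | yes |

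No missing-data rule fills the gap. In the section Statistical analysis, the primary logistic regression carries none; last observation carried forward appears in the sentence on the within-group analysis of the experimental arm. Table 3 first schedules CGI-I at T1, so a person leaving before week 5 has no CGI-I to carry forward.

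**2. The plan's own power figure**

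Inputs (sections Statistical analysis, and Randomization and study intervention): 180 participants, 1:1, so 90 per arm; control response 20%; odds ratio 2.55; significance level 0.05; stated power 90%.

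- Treated odds = (0.20/0.80) × 2.55 = 0.6375, so the treated rate = 0.6375/1.6375 = 0.3893.
- Power = Φ{[d − 1.96·√(2p̄(1−p̄)/n)] / √([p₁(1−p₁) + p₂(1−p₂)]/n)}, with d = 0.1893 and p̄ = 0.2947.
- n = 90: (0.1893 − 0.1332)/0.0665 = 0.844, giving 80.1%.

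The stated 90% is not reproduced: two-sided power is 80.1%, one-sided 87.8%. That is a separate issue; here it only means that the baseline for counting losses is about 80%.

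**3. Loss of precision**

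The documents give no dropout rate and no dropout allowance, since 180 is both the recruitment target and the number in the power statement. Equal losses in both arms are therefore assumed over a range.

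| Loss in each arm | Evaluable per arm | Two-sided power |
|---|---|---|
| 0% | 90 | 80.1% |
| 5% | 85.5 | 78.0% |
| 10% | 81 | 75.7% |
| 15% | 76.5 | 73.3% |
| 20% | 72 | 70.7% |

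At 15%: (0.1893 − 0.1445)/0.0721 = 0.622, giving 73.3%. If the test were one-sided, the same loss would take 87.8% to 82.7%.

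**4. Possible bias**

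Assume no treatment effect (20% response, 18 of 90 in each arm), every leaver a non-responder, and a complete-case analysis.

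- 20% of the synbiotic arm leaves (18 people): 18/72 = 25.0%.
- 10% of the placebo arm leaves (9 people): 18/81 = 22.2%.
- Difference +2.8 points; odds ratio (0.250/0.750)/(0.222/0.778) = 1.17; rejection rate about 6.9% against a nominal 5%.

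Other assumed losses under the same model: 15% versus 5% gives odds ratio 1.15 and 6.7% rejection; 30% versus 10% gives 1.40 and 14.3%; 10% versus 10% gives 1.00 and 5.0%.

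If leavers are instead counted as non-responders, the rates return to 18/90 = 20% in both arms.

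**The case against.** The other side has several good points.

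- **Non-collection is inferred.** The article does not forbid CGI-I and ARI-S at the closing visit. T3 is given a safety aim in the Participant timeline, yet Table 3 marks both scales there, so a safety purpose does not exclude them. This stands. It does not supply a week-10 assessment for leavers, because the text neither lists scales for that visit nor ties it to week 10.
- **The rules are softer than they may look.** Exit after an adverse event is discretionary, deterioration may lead only to a discussion, and Table 1 excludes major gastrointestinal illness, not ordinary gastrointestinal symptoms. Only other exclusion violations bring certain exit. This stands, and limits how many may leave.
- **A full protocol exists and may add detail.** The article cites version 2.0, which is not shown, and missing-data handling may sit in an analysis plan. The point is therefore confined to what the article states: rules that end study participation, with contacts afterwards that include no week-10 outcome.
- **The bias example is conditional.** It needs unequal loss, all leavers non-responders and a complete-case analysis, which the article does not specify. Counting leavers as non-responders removes it. Those who leave after T1 also have a week-5 value, although no rule says it serves for the primary outcome.

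A reader might infer that leavers are seen only once, that their outcomes are deliberately not collected, or that no analysis could repair the result. The article supports none of these: adverse events are followed to resolution or stability, it is silent on which scales are taken at the closing visit, and the example itself is repaired by a non-responder rule.

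**Conclusion.** The point holds in this form: as written, stopping the product and leaving the study are one step, and no week-10 CGI-I or ARI-S is provided for those who take it. Because the triggers can depend on treatment and on response, the primary outcome may be informatively missing.

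The size is not known from the document. Under assumed losses of 20% versus 10%, all non-responders, and a complete-case analysis, a null effect would appear as +2.8 points. With equal loss there is no bias under this model, only lower power: from about 80% to 73% at 15%. That fall would follow from any 15% loss, including withdrawals of consent. It is a moderate weakness of data collection, not proof that the result would be biased.

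**What to change.** Leave the clinical rules on who stops exactly as they are, and change only what is collected afterwards.

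1. State that stopping the product and withdrawing from the study are separate decisions.
2. Invite participants who stop but still consent to the scheduled T1 and T2 assessments of CGI-I and ARI-S.
3. At minimum, collect both scales at the follow-up visit already planned, and record its timing, since it will not be a week-10 value unless it falls then.
4. Analyse all randomized participants in their allocated arm.

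The cost is a short amendment and some extra T1 and T2 visits. The minimum option adds two scales to a visit that already takes place; for comparison, T3, which carries both scales, is planned at about 20 minutes. Outcomes of those who revoke consent remain unrecoverable.

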### Data management

Participants and clinical staff will be able to fill out all requested questionnaires online via the Castor database system (http://castoredc.com/). Then, data will be directly uploaded to a central database using a macro software. Both the Castor database system and macro software are fully secure and in accordance with current standards (i.e., Good Clinical Practice [GCP], 21 CFR Part 11, EU Data Protection Directive, ISO27001 and ISO9001 hosting). Both systems are also approved by the Clinical Research Centre Nijmegen, Nijmegen, The Netherlands, because it will be responsible for tracking any changes made manually to raw data. Any other data will be uploaded (after site-specific quality control) by the research team to the central database using encrypted mass storage devices. All information collected in the study will be coded with a unique pseudocode identifier (PSC) in such a way that participants cannot be identified from the corresponding data (directive 95/46/EC) and ensuring that the information collected for the study remains strictly confidential. Likewise, collected samples of biomaterial (i.e., blood and microbiota) will be labeled with the corresponding PSC. All patient-related data will be stored at the clinical sites in a database with password protection. A separate single database on the central server of VHIR will link the PSC to the participant’s personal data (including name, address, telephone details, and date of birth). Databases will be accessible only to the immediate research team at each site.

